## Abstract

**Background:**

Eating problems frequently affect quality of life and physical, psychological and social function in patients treated for head and neck cancer (HNC). Residential rehabilitation programmes may ameliorate these adverse effects but are not indicated for all individuals. Systematic assessment of rehabilitation needs may optimise the use of resources while ensuring referral to rehabilitation for those in need. Yet, evidence lacks on which nutrition screening and assessment tools to use. The trial objectives are: 1) To test the effect of a multidisciplinary residential nutritional rehabilitation programme compared to standard care on the primary outcome body weight and secondary outcomes health-related quality of life, physical function and symptoms of anxiety and depression in patients curatively treated for HNC and 2) To test for correlations between participants’ development in outcome scores during their participation in the programme and their baseline scores in Nutritional Risk Screening 2002 (NRS 2002), the Scored Patient-Generated Subjective Global Assessment Short Form (PG-SGA SF), and M. D. Anderson Dysphagia Inventory (MDADI) and to assess sensitivity, specificity and predictive values of the three tools in relation to a clinically relevant improvement in outcome scores.

**Methods:**

In a randomised controlled trial, 72 patients treated for HNC recruited through a nationwide survey will be randomised to a multidisciplinary residential nutritional rehabilitation programme or to a wait-list control group. Data are collected at baseline, three and six months. Primary outcome is change in body weight, and secondary outcomes include changes in quality of life, physical function and symptoms of anxiety and depression. Potential correlations between intervention effect and baseline scores in NRS 2002, PG-SGA-SF and MDADI will be tested, and sensitivity, specificity and predictive values of the three tools in relation to a clinically relevant improvement in outcome scores will be assessed.

**Discussion:**

This is the first randomised controlled trial to test the effect of a multidisciplinary residential nutritional rehabilitation programme in patients treated for HNC. Recruitment through a nationwide survey gives a unique possibility to describe the trial population and to identify potential selection bias. As the trial will explore the potential of different nutrition screening and assessment tools in the assessment of rehabilitation needs in patients treated for HNC, the trial will create knowledge about how selection and prioritisation of nutritional rehabilitation aimed at patients treated for HNC should be offered. The results may contribute to a better organisation and use of existing resources in benefit of patients treated for HNC.

**Trial registration:**

The trial is registered by The Danish Data Protection Agency (registration 2012-58-0018, approval number 18/14847) and the Regional Committees on Health Research Ethics for Southern Denmark (journal number 20182000–165). ClinicalTrials.gov Identifier: NCT03909256. Registered April 9, 2019.

## Background

The incidence of head and neck cancer (HNC) has increased to approximately 900.000 new cases worldwide in 2018 [1, 2]. With a simultaneous increase in the relative survival [3], the population of patients treated for HNC is increasing.

Many patients treated for HNC feel unprepared for the life that awaits them after cancer treatment [4–7] when eating problems and other late effects may persist for years or even become chronic [8]. These include dysphagia (swallowing difficulties), xerostomia (dry mouth), dysgeusia (taste disturbances), and trismus (reduced mouth opening) [8]. The negative effects of eating problems on quality of life (QOL) and everyday life in patients treated for HNC have been documented in quantitative [8–13] and qualitative [5, 14–19] studies. Based on existing studies [4–7, 18, 20, 21] it is suggested that appropriate rehabilitation services can strengthen the patient’s ability to cope with eating problems and thereby reduce the negative consequences. Yet, unmet rehabilitation needs are widely documented in this population [4, 5, 7, 16, 22, 23].

A frequent strategy for patients treated for HNC to cope with eating problems is the trial-and-error approach [4, 6, 16, 20] with continuous experiments to find tolerated foods as this varies over time. The process may be complicated by fear of choking [4, 15, 19] and feelings of defeat when experiments are unsuccessful [4, 16]. Residential group based rehabilitation programmes, where the daily meals are part of the intervention, may be particularly effective to support patients treated for HNC in this coping process as they can provide a safe environment to practice eating skills [4, 21]. High participant satisfaction and improvements in QOL scales were seen among patients treated for HNC participating in a pilot study testing a 1-week residential psychoeducational programme [21]. In another pilot study, qualitative data showed that patients treated for HNC benefitted from participating in a multidisciplinary residential nutritional rehabilitation programme [4]. Unpublished quantitative data from the latter pilot study (included in Additional file 1) showed significant improvements in body weight and several QOL scales at 3-month follow-up. With no control group in the pilot study, the results should be tested in a randomised controlled trial on the effect of the multidisciplinary residential nutritional rehabilitation programme.

The increasing population of patients treated for HNC may present a challenge to existing health care systems through increased rehabilitation costs. Residential rehabilitation programmes and other specialised rehabilitation services aimed at eating problems may be costly, and may not be indicated for all patients treated for HNC. Systematic screening and/or assessment of rehabilitation needs in patients treated for HNC may optimise the use of existing resources while ensuring referral to appropriate rehabilitation services for those in need.

The European Society for Clinical Nutrition and Metabolism recommends that nutritional screening is performed at cancer diagnosis and repeated regularly depending on the stability of the clinical situation [24]. Several tools have been developed to screen and assess nutritional risk, nutritional status and nutrition impact symptoms [24–28]. Nutritional Risk Screening 2002 (NRS 2002), [26] is validated to identify patients, regardless of their diagnosis, who will benefit from nutritional intervention. Yet, to our knowledge no studies have validated NRS 2002 in patients treated for HNC after treatment, and even for patients with HNC prior to treatment, it has been suggested to use a modified version with a different cut-off value [29]. Furthermore, NRS 2002 only assesses dietary intake as the consumed amount in relation to requirements [26]. It does not assess nutrition impact symptoms, which would be highly relevant in this population. The Scored Patient-Generated Subjective Global Assessment Short Form (PG-SGA SF) includes information on nutrition impact symptoms and changes in dietary intake (amount or consistency) in the assessment of nutritional risk and nutritional deficit [27], but no validation studies have been carried out in patients after treatment for HNC. The M. D. Anderson Dysphagia Inventory (MDADI) [28] is developed to assess dysphagia-specific QOL in patients with HNC. But so far, no clinical studies have investigated associations between MDADI score and intervention effect. Hence, the evidence is scarce on the three tools’ ability to identify patients treated for HNC who will benefit from posttreatment nutritional rehabilitation.

### Trial objectives

The objectives of the trial are:
To test the effect of a multidisciplinary residential nutritional rehabilitation programme compared to standard care on the primary outcome body weight and secondary outcomes health-related QOL, physical function and symptoms of anxiety and depression in patients curatively treated for HNCTo test for correlations between participants’ development in outcome scores during their participation in the programme and their baseline scores in NRS 2002 [26], PG-SGA SF [27], and MDADI [28] and to assess sensitivity, specificity and predictive values of the three tools in relation to a clinically relevant improvement in outcome scores

## Methods

### Trial design

The trial is a randomised controlled trial with recruitment through a nationwide survey. Participants will be randomised into either an intervention group or a wait-list control group. Data will be collected at baseline, at three, and at six months (Fig. 1).

**Fig. 1 Fig1:**
[figure not shown]
Timeline of the NUTRI-HAB trial

Differences between groups at 3-month follow-up will be tested to assess the effect of the intervention. Exploratory analyses will be based on all data collected from baseline to 6-month follow-up. They will include analyses of the long-term effect of the intervention and of whether the selected nutrition screening tools are labile and able to reflect changes over time.

The SPIRIT (Standard Protocol Items for Randomized Trials) 2013 [30, 31] statement, the CONSORT (Consolidated Standards of Reporting Trials) extension for reporting trials of nonpharmacologic treatments [32] and the TIDieR (template for intervention description and replication) [33] checklist and guide have been used as guidelines for developing the trial protocol. The SPIRIT checklist is included in Additional file 2, and descriptions of all physical and informational materials used in the trial and how to assess these are included in Additional file 3.

### Setting

The trial will be carried out at REHPA, the Danish Knowledge Centre for Rehabilitation and Palliative Care in Nyborg, Denmark, between May 2019 and December 2019.

In Denmark, cancer treatment and rehabilitation are funded by government taxes and free of charge for patients. While cancer treatment and rehabilitation services during treatment are offered at the hospitals, posttreatment rehabilitation is primarily a municipal responsibility [34]. Denmark comprise 98 municipalities with great variation between their rehabilitation services [35, 36]. Only 17 Danish municipalities offered diagnosis specific rehabilitation services for patients treated for HNC in 2017 [36]. Hence, the level of rehabilitation that participants have received prior to their participation in the trial may vary, and information on which rehabilitation services participants have been offered and participated in will be registered.

### Participants

Participants will be recruited among respondents of a nationwide survey on late effects and health-related QOL in Danish patients treated for HNC 1–5 years following radiation therapy. The survey population was identified through The Danish Head and Neck Cancer Group’s (DAHANCA) national clinical quality database [37].

The survey was distributed in March 2019. Patients treated for HNC will be eligible for participation in the trial if they meet the following inclusion criteria:

Register-based information:
Have been diagnosed with cancer of the larynx, pharynx, or oral cavityHave completed curatively intended treatment with radiation therapy 1–5 years before survey distribution (1st of March 2014 to 28th of February 2018)Are aged ≥18 years

Self-reported information collected through the survey:
Have no active HNC or any other active cancer at the time for completion of the surveyAre self-reliant. Survey respondents are defined as self-reliant if they answered “Not at all” on the question “Do you need help with eating, dressing, washing yourself or using the toilet?” in The European Organization for Research and Treatment of Cancer’s (EORTC) QLQ-C30 questionnaire [38] on health-related QOLAre able to speak and understand DanishHave confirmed that they are interested in participating in a multidisciplinary residential nutritional rehabilitation programme at specific dates and given their permission to be contacted with further information. This inclusion criterion has been established to obtain permission and contact details for telephone contact and to narrow down the population for inclusion since the nationwide survey was distributed to almost 2000 individuals. By giving survey respondents the possibility to opt out for further contact regarding the trial, we reduce the number of inquiries to each respondent.

Potential recurrence of cancer during the trial will not lead to exclusion of participants. In the event of cancer recurrence in one or more participants, sensitivity analyses will be made to investigate whether this affects the trial results.

### Intervention

The intervention is a multidisciplinary residential nutritional rehabilitation programme with a primary focus on the physical, psychological and social aspects of eating problems after treatment for HNC. The programme will comprise five days initial residential stay and two days follow-up residential stay after three months (Fig. 1). The rehabilitation centre has developed a core programme model through available evidence and more than 10 years’ experience in offering multidisciplinary residential rehabilitation programmes for heterogeneous groups of patients with cancer [39, 40]. To meet the specific rehabilitation needs of patients treated for HNC, the core programme was further developed through available evidence, patient involvement and a pilot study including 40 patients treated for HNC [4]. Components of the rehabilitation centre’s core programme will be included even though they are not specifically aimed at eating problems. Yet, these activities have shown to be relevant and beneficial to other groups of patients with cancer [39–41]. The programme consists of group sessions with patient education and a few individual activities. The content of these sessions and activities are shown in Table 1 while a detailed schedule of the programme is shown in Additional file 4.

**Table 1 Tab1:** Patient education sessions in the multidisciplinary residential nutritional rehabilitation programme [42] in the NUTRI-HAB trial

SESSION	DURATION (minutes)	CONTENT	SESSION LED BY
Welcome session with presentation of the programme^a,d^	30	The aim of the welcome session is to make participants feel safe and comfortable in the environment in which they will be spending the next five days. This may contribute to increased motivation and willingness to participate actively throughout the programme [43, 44].	Course leader^f^ and clinical dietitian
Presentation round^a,d^	60	In the presentation round, participants will share information about their background and cancer diagnosis, and they will be encouraged to use selected picture cards to narratively describe their expectations and desired outcomes of participation. The aim of the session is to enhance group formation and to establish a sense of community among participants since this may facilitate patient empowerment [45]. Central staff members (course leader, physician, clinical dietitian, and evening hostess) participate.	Course leader
Social activity^a,d^	60	A social activity including music and movement will be scheduled on the first evening of the programme to support group formation and candidness among participants.	Music therapist
Theoretical session on eating problems^a,d^	105	The session will include dietary advice to manage different nutrition impact symptoms e.g. choice of foods, texture and flavour modification [24, 46]. Exchange of experiences between participants will be encouraged.	Clinical dietitian
Individual dietary counselling^c,d,e^	30 (20 at follow-up)	In the individual dietary counselling, dietary advice will be tailored to the individual participant [24].	Clinical dietitian
Practical kitchen workshop^b,d^	180	In the practical kitchen workshop, participants will prepare foods of different textures and flavours, and take-home recipes will be handed out. The aim of the workshop is to inspire and put theory into practice [4], and practical kitchen sessions have supported dietary changes in studies with other types of cancer survivors [47, 48].	Clinical dietitian
Swallowing exercises^b,d^	90	Participants will be instructed in different swallowing exercises and exercises for jaw and tongue mobility, since these types of exercises may reduce dysphagia and trismus [46, 49]. Participants will receive an exercise manual and a training diary, and will be encouraged to continue doing the exercises, when they come home.	Occupational therapist
Dental problems and oral hygiene^b,d^	75	Dental problems are frequent after treatment for head and neck cancer [22]. The session will include information on how to maintain good oral hygiene and on dental reimbursement rules in relation to cancer treatment.	Dental hygienist
Physical activity^a,d,e^	75	Physical activity may contribute to ameliorate late effects associated with decreased physical function in cancer survivors [50–53]. In the physical activity sessions, participants will be introduced to different kinds of physical activity that they can do at home e.g. balance or resistance training exercises. Exercises will be adjusted to the participants’ training level.	Physiotherapist
Yoga^b,d^	60	Yoga may contribute to improve quality of life and to reduce fatigue and symptoms of distress and anxiety in cancer survivors [54, 55]. The yoga session will be based on principles from Hatha yoga and Physioflow yoga. Special attention will be given to exercises aimed at releasing tensions in the head and neck area.	Physiotherapist certified as yoga instructor
Psychological reactions to cancer^b,d^	150	The session will be based on a psychoeducational approach [56, 57] and will aim at supporting participants’ coping of everyday life after cancer. The session will comprise psychologist’s presentation of frequent psychological reactions to cancer and discussions in small groups.	Psychologist
The existential dimension of rehabilitation^a,d^	90	The session is a group conversation on questions of existential and spiritual character that often follow the diagnosis of a life-threatening disease [58, 59].	Priest
Massage therapy^c,d^	45	Massage therapy may contribute to short term reduction of pain and anxiety even though the level of evidence is very low [60]. Each participant will receive 45 min of relaxing massage therapy and will have to choose between a full body relaxing massage or special attention given to a certain area e.g. tensions in the neck.	Massage therapist
Vocational counselling^b,d^	75	Optional session. Vocational counselling session will aim to support return-to-work processes and hence participants functioning in accordance with the World Health Organization’s International Classification of Functioning, Disability and Health (ICF) [61]. The session will include information on rights and obligations according to Danish legislation.	Social worker
Fatigue and sleep problems^b,d^	75	Optional session on reasons for and management of cancer-related fatigue [52, 62] and sleep problems [63, 64].	Nurse
Motivation, goal setting and action plans^a,d^	100	Based on principles of motivational interviewing [65], the session will allow participants to reflect on, how they will implement new inspiration and knowledge gained through the programme, when returning back home.	Course leader
Intimacy and sexuality^b,e^	90	Optional session. Based on the PLISSIT model [66], the session will address how sexuality and intimacy can be affected by cancer and cancer treatment [67, 68] and provide advice for management of potential challenges. Participants will be divided into groups by gender for the session.	Sexologist
Meaning and values in life^b,e^	90	Optional session. Based on principles of acceptance and commitment therapy [69], the session will aim to support participants in re-establishing meaning in life through reflections on values and sources to meaning in lif e[70, 71].	Psychologist
Individual counselling^c,d,e^	30–45	Individual counselling with relevant health professionals (e.g. speech pathologist, physician) will scheduled depending on participants’ needs.	Depending on need

^a^ Group session with a maximum of 20 participants; ^b^ Group session with a maximum of 10 participants; ^c^ Individual session; ^d^ Session is offered at the initial five days residential stay; ^e^ Session is offered at the two days follow-up residential stay after three months; ^f^ Course leader (nurse, physiotherapist or social worker) coordinates all activities during the week and is the participants’ primary contact person

Rehabilitation Centre Dallund and REHPA, The Danish Knowledge Centre for Rehabilitation and Palliative Care have developed the core model for the residential group-based rehabilitation programme as a best practice patient-centred rehabilitation model for heterogeneous groups of cancer survivors. The rationale, evidence base and content of the model and the specific activities are described in details elsewhere [42]. The core model has been adjusted to meet the rehabilitation needs of the population in the NUTRI-HAB trial

As described in the background section, patients treated for HNC frequently use the trial-and-error approach [4, 6, 16, 20] to cope with their eating problems. The programme aims to support participants in this coping process in various ways. Participants will stay at the premises during the residential stays and all meals will be served in the dining room and break areas. Meals will be served as self-service buffets, and foods of different textures and flavours will be served to inspire and to allow participants to experiment. The menu plan for the entire residential stay will be presented on the first day and will be available in the dining room. If a participant has specific dietary preferences or requirements that are not met in the menu plan for a given meal, the kitchen staff will find alternatives together with the participant. The meals are furthermore intended as social training since eating problems often lead to social withdrawal [4, 15, 17, 20]. Individual counselling sessions with relevant professionals (e.g. speech pathologist or physician) will be scheduled depending on the individual participant’s needs assessed by baseline questionnaires and outcome data.

Between the initial stay and the two days follow-up, participants will have two telephone consultations with a clinical dietitian. These will be scheduled in week 4 and week 8. The aims of these consultations are to follow up on topics addressed in the individual consultation at the residential stay, to answer potential questions that have emerged, and to encourage the participant to continue with any activities or changes that they planned to implement after the residential stay.

The programme will be free of charge for participants and an additional offer to existing rehabilitation services. Participants will be asked to fill out an evaluation form in which they will evaluate the overall residential stay, the different sessions and indicate whether they participated in the specific session.

### Wait-list control group

Between baseline and 3-month follow-up, the wait-list control group will receive no intervention other than standard care. Since participants will be from all over the country, standard care may vary. Participants will not be restricted from participating in other rehabilitation services during the trial period. After 3-month follow-up, participants in the wait-list control group will be offered participation in the multidisciplinary residential nutritional rehabilitation programme.

### Inclusion and randomisation

Figure 2 shows the flow of the inclusion and randomisation process. Individuals who have responded to the nationwide survey within nine weeks from survey distribution and who meet the inclusion criteria will be randomised into invitation lists for intervention group or wait-list control group. The allocation ratio will be 1:1, and allocated individuals will be placed in random order on the numbered invitation list. Four residential rehabilitation programmes are scheduled, and each has a maximum capacity of 20 participants. Hence, a maximum of 40 participants in each group can be included. The first 40 individuals on each invitation list will receive further information about the trial and be invited to participate. Invitations will be sent electronically to e-Boks, a secure digital mailbox linked to the individual’s civil registration number. In Denmark, it is mandatory to have e-Boks unless a citizen applies for exemption. Individuals without e-Boks will receive the invitation through postal mail. If the invitation is declined, the next person on the given invitation list will be invited. If invited individuals do not respond, they will be contacted by telephone.

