**Fig. 2 Fig2:**
[figure not shown]
Flow chart of the NUTRI-HAB trial

Randomisation will be stratified by need for rehabilitation services measured by the REHPA scale adapted from the National Comprehensive Cancer Network® Distress Thermometer [72]. On the REHPA Scale, participants indicate how close or how far they are from living the life they want after or in spite of their disease. A higher score indicates greater rehabilitation needs. The REHPA Scale was included in the nationwide survey. A certain score on the REHPA scale is not an inclusion criteria for the present trial, but randomisation will be stratified to ensure similar proportions of individuals with a score of ≥3 across the invitation lists. Participants will be randomised in STATA/IC 15.1 by a blinded researcher ([name]) who is not involved in the trial intervention or assessment of outcomes.

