### Data analysis

The statistical analysis plan for the trial is shown in Additional file 5. Data will be analysed in SAS® Enterprise Guide® 7.1 by both per protocol and intention-to-treat principle [85]. Data analyses will not be commenced until all data collection is completed. A blinded researcher ([name]) will analyse the data, and the project group will interpret results before unblinding. Development in outcome scores from baseline to 3-month follow-up will be calculated for each participant, and differences between intervention group and wait-list control group will be tested using a two-sample two-sided t-test for normally distributed data and Mann-Whitney U test for non-normally distributed data. A significance level of 5% will be applied. Effect size will be estimated with Cohens d [86]. Multiple linear regression will be used to assess the influence of potential confounding variables (e.g. time interval from completion of treatment) on intervention effect. Mean baseline values for outcome scores in both groups will be presented in result tables. Simple linear regression will be used to test correlations between developments in outcome scores and baseline scores in NRS 2002, MDADI or PG-SGA SF. Sensitivity, specificity and predictive values of different cut-offs in NRS 2002, MDADI or PG-SGA SF at baseline in relation to a clinically relevant improvement in outcome scores during participation in the programme will be assessed. To avoid missing data, participants who drop out of the trial will be encouraged to participate in follow-up measurements. The percentage and patterns of missing values in outcome variables will be examined. If data are missing at random and the percentage of missing data is not substantial [87], multiple imputation techniques will be used in the intention-to-treat analyses.

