## Ethics and dissemination

The trial will be conducted in accordance with the Declaration of Helsinki [88]. Informed written consent will be obtained from all participants before inclusion. Participants will be informed verbally and in writing that participation is voluntary, and that they can withdraw their consent at any time. Participants will receive no payment for their participation, and their only expenses associated with participation will be transportation costs to the rehabilitation centre. For ethical reasons, we will use a wait-list control group, who also receives the intervention after 3-month follow-up. Based on the prior pilot study [4] it is expected that participants will benefit from participation, and there are no expected risks associated with participation. The Regional Committees on Health Research Ethics for Southern Denmark have assessed the duty to notify for the present trial (journal number 20182000–165). Based on Danish legislation, the committees concluded that the trial is not subject to the duty to notify since no biological material is included. The trial is registered by The Danish Data Protection Agency, registration number 2012-58-0018, approval number 18/14847, and registered in the database Clinical Trials (www.clinicaltrials.gov, NCT03909256). Amendments to the protocol will be made public at clinicaltrials.gov.

Results will be published in international peer-reviewed journals and presented at national and international conferences.

Within the confines of Danish legislation, anonymised data from the trial will be available for other researchers upon reasonable request when results have been published.

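### Respondents are randomised to arm-specific invitation lists before they are invited or consent, and decliners are replaced within the arm, so entry to the trial can depend on allocation

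*Protocol article*

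**What the plan says.** The order of events is set out under Inclusion and randomisation. Respondents who replied within nine weeks and "who meet the inclusion criteria will be randomised into invitation lists for intervention group or wait-list control group". The lists are built as follows: "The allocation ratio will be 1:1, and allocated individuals will be placed in random order on the numbered invitation list". Information about the trial comes next: "The first 40 individuals on each invitation list will receive further information about the trial and be invited to participate". Refusals are expected and handled within the arm: "If the invitation is declined, the next person on the given invitation list will be invited". Non-responders are telephoned.

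The same section stratifies on the REHPA scale: "randomisation will be stratified to ensure similar proportions of individuals with a score of ≥3 across the invitation lists". Ethics and dissemination adds: "Informed written consent will be obtained from all participants before inclusion". Data analysis says the data will be analysed "by both per protocol and intention-to-treat principle".

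Three other sections describe what each arm is being asked to accept:
- **Intervention:** the programme opens with a five-day residential stay.
- **Wait-list control group:** these participants have standard care only until the 3-month follow-up and are offered the programme after it.
- **Outcome measures and data collection:** control participants have their baseline measurements at a regional outpatient clinic, whereas intervention participants have theirs at the rehabilitation centre.

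Before randomisation, the Participants section requires only that respondents have declared interest in the programme on specific dates and agreed to be contacted.

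**The concern.** Randomisation makes two groups comparable at the moment of allocation. They stay comparable at entry only if entry does not depend on the arm. Here the decision to take part is made after allocation, and the two offers differ: one is a residential stay now, the other a clinic visit now with the stay about three months later. Someone with pressing eating problems, or with work or family commitments, may accept one and refuse the other.

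If such reasons are related to later weight change, the acceptors differ between arms before treatment starts. The difference is then confounded with the treatment effect on the primary outcome. Filling each vacancy from the same list keeps the numbers up but draws the replacement through the same arm-specific filter. A larger trial would not shrink the bias, and it cannot be undone once recruitment has finished.

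**Working it through.** **1. The plan's own figure.** Sample size gives a mean weight change of 1.74% with SD 2.37%, 80% power and 5% significance; Data analysis specifies a "two-sample two-sided t-test for normally distributed data and Mann-Whitney U test for non-normally distributed data". By the normal approximation, n = 2 × [2.37 × (1.960 + 0.842) / 1.74]² = 29.1, rounded up to 30 per group. Solving with the t distribution gives 30.1, and power at 30 is 79.8%. With 15% withdrawal, 30 / 0.85 = 35.3, so 36 per group and 72 in total. The stated figures reproduce and are not in dispute.

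**2. Order of events.** Read together, the sections give: survey interest, allocation to an arm's list, trial information and invitation, acceptance or refusal, consent, baseline. Every step from invitation onward is taken within an arm.

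**3. Who is lost.**
- *People low on the list who are never invited.* Each list is in random order, so they are a random remainder. Leaving them out causes no bias.
- *People invited who decline.* They leave by choice, after allocation, probably knowing the arm. They are never weighed at baseline, so a percentage change from baseline cannot be observed for them. This is the group that matters.

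**4. Do other provisions repair it?** Stratification balances REHPA need across the lists, not among acceptors. An independent randomiser and a blinded analyst do not affect who accepts. The 15% allowance covers withdrawal of included participants. Multiple imputation is described for missing outcome values; the article does not provide for randomised people who declined.

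**5. Size, under assumptions.** The documents give neither acceptance rates nor their relation to weight change. Suppose acceptance follows a standard normal latent trait, with those highest on it accepting, and the trait has correlation r with percentage weight change. With acceptance rate a, the mean trait among acceptors is m(a) = φ(z) / a, where φ is the standard normal density and z is the point exceeded with probability a. Then bias = r × 2.37 × [m(lower rate) − m(higher rate)].

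m(0.4) = 0.97, m(0.5) = 0.80, m(0.7) = 0.50, m(0.8) = 0.35, m(0.9) = 0.195.

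| Acceptance in the two arms | Difference in m | Bias, r = 0.2 | Bias, r = 0.3 | Share of 1.74 |
|---|---|---|---|---|
| equal | 0 | 0 | 0 | 0% |
| 80% vs 90% | 0.155 | 0.07 | 0.11 | 4–6% |
| 70% vs 90% | 0.30 | 0.14 | 0.21 | 8–12% |
| 50% vs 80% | 0.45 | 0.21 | 0.32 | 12–18% |
| 40% vs 80% | 0.62 | 0.29 | 0.44 | 17–25% |

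The direction depends on which arm has the lower acceptance and on the sign of the correlation; neither is known.

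**6. Effect on the test.** With no true effect and 30 analysed per arm, the standard error is 2.37 × √(2/30) = 0.61. A bias of 0.25 points raises the two-sided 5% error rate to 6.9%, and a bias of 0.5 points raises it to 12.7%.

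**7. Number randomised.** The abstract says that 72 patients will be randomised. Inclusion and randomisation allocates every eligible respondent, and Sample size uses 36 per group as the number to include. These describe two different populations.

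**The case against.** The case on the other side has real force.

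- **Refusals may be few and similar.** Everyone on either list has already declared interest in this programme on specific dates, both arms are eventually offered it, and non-responders are telephoned. This stands as mitigation. It does not remove the problem, since the plan itself provides for refusals and replacement.
- **Disclosure is inferred.** The invitation letter and the flow chart are not shown, and the article does not say that the letter names the arm. A reader might infer that disclosure is a stated feature of the design; it is not. It is likely, because start date and baseline site differ by arm, and nothing says allocation is withheld until consent.
- **The analysis set may be defined elsewhere.** The analysis plan is in Additional file 5, which is not shown, so a missing definition of intention-to-treat is no fault here. But the order of allocation, invitation and replacement is fixed in the article, and an analysis plan cannot supply observed baseline weights for people who declined.
- **Some protection exists.** The outcome is change within a person, baseline values will be tabulated by group, regression will examine potential confounders, and the survey data are held. These help to detect or reduce imbalance on measured factors, but not on unmeasured motivation. The Discussion's remarks on selection bias concern the trial population as a whole, not a difference between arms.
- **The size rests on assumption.** This is correct, and small acceptance gaps give small biases.

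**Conclusion.** The concern holds as a risk to the primary comparison. Allocation precedes information and consent, refusals are replaced within the arm, and the two offers differ, so comparability at entry rests on an untested assumption about acceptance instead of on randomisation. An intention-to-treat analysis of included participants does not cover the randomised people who declined.

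Two stronger readings are tempting. One is that the groups are shown to be biased. The documents do not support this: bias requires acceptance to differ by arm in a way related to weight change, and it is zero if acceptance depends on the same factors at the same rate in both arms. The other is that everyone randomised but not included damages the comparison. That is wrong for people never invited, because the lists are randomly ordered.

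Under the latent-trait assumption (correlation 0.2 to 0.3, SD 2.37), the bias runs from about 0.07 percentage points at 80% versus 90% acceptance to 0.44 at 40% versus 80%, that is, 4% to 25% of the planned 1.74. The true value cannot be computed from the documents.

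**What to change.** Place all eligible, interested respondents on one randomly ordered list. Send one common letter that explains both arms and gives both sets of dates. Obtain written consent, then randomise consenters 1:1 within REHPA stratum. Those who decline do so before allocation and cannot unbalance the arms.

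The cost is protocol wording and a revised letter, with no added patients or visits. Participants must be available for either set of dates, so some may decline. A short step is also added to a tight schedule: responses are accepted for nine weeks after the March 2019 survey, and the trial starts in May 2019.

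If the two lists must stay:
- use an identical invitation that conceals allocation until consent is signed;
- report the numbers invited, declining and accepting by arm;
- compare acceptors between arms on the survey data already held;
- state that the analysed set is not all randomised people.

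In either case, reconcile the abstract's statement that 72 patients will be randomised with the text under Inclusion and randomisation, so that the numbers randomised and included are each clear.
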